#### Secondary outcomes

The secondary outcome for the effectiveness component of this trial of the present study is sleep-related impairment (SRI), measured using the Patient-Reported Outcomes Measurement Information System (PROMIS) Sleep-Related Impairment (computer adaptive test [CAT] Version) [30]. The SRI is automatically converted into T-scores and standard errors which have a general adult population mean of 50. As the SRI is measured using CAT, missing individual items are not allowed in Research Electronic Data Capture (REDCap) so it will either be complete or missing. Both pregnancy and postpartum endpoints will be applied for SRI in the same way as described for ISI above.

#### Health economic outcomes

The primary outcome for the economic evaluation will be total quality-adjusted life-years (QALYs) in the birthing parent *and* infant from baseline to 24 months postpartum based on the following:*Parent quality of life*, as measured by total continuous QALYs from baseline (T1) to 24 months postpartum (T6), calculated based on Assessment of Quality of Life four dimension (AQoL-4D) index scores [31] in the main analysis. The AQoL-4D measures health-related quality of life on four dimensions: *independent living*, *social relationships*, *physical senses*, and *psychological well-being**Parent quality of life*, as measured by total continuous QALYs from baseline (T1) to 24 months postpartum (T6), calculated based on PROMIS-Preference (PROPr) scores [32] for sensitivity analysis. The PROPr reflects seven PROMIS domains: cognitive Function (CAT Version) [33], Depression (CAT Version) [34], Fatigue (CAT Version) [35], Pain Interference (CAT Version) [35], Physical Functioning (CAT Version) [35], Sleep Disturbance (CAT Version) [30] and the Ability to Participate in Social Roles (CAT Version) [35]*Infant quality of life*, as measured by total QALYs from birth (T3) to 24 months (T6), calculated based on parent completion of the Infant Quality-of-Life Instrument (IQI) [36, 37]

The secondary outcome for the economic evaluation will be the primary clinical outcome during the postpartum period (average ISI during the postpartum period T3–T5), representing overall symptom burden for the birthing parent.

Results from the economic evaluation will be expressed as (1) cost per QALYs gained and (2) cost per point improvement on the primary clinical outcome where costs will encompass direct cost of the intervention, health service costs, and productivity costs as follows:*Intervention costs* to 24 months postpartum for the *Healthy Sleep Program* and usual care*Health service costs* from baseline to 24 months postpartum, calculated from parent self-report of health service utilisation for both birthing parent and infant*Productivity costs* from baseline to 24 months postpartum, as measured by the Work and Productivity and Activity Impairment (WPAI) scale [38] for insomnia

#### Implementation outcomes

*Adverse events*, as measured by Adverse Event Checklist [39] at T2–T6.*Barriers and enablers to sustained implementation*, explored through qualitative semi-structured interviews with treating clinicians, participants and their partners, and other relevant stakeholders (e.g. obstetricians and gynaecologists, general practitioners, midwives, psychologists) guided by the Theoretical Domains Framework (TDF) [40] and the Practical Robust Implementation and Sustainability Model (PRISM) [41]*Satisfaction with intervention*, as measured by Client Satisfaction Questionnaire at T4 [42]

#### Exploratory outcomes

*Sleep duration, quality and characteristics*, measured using adapted Consensus Sleep Diary at T1–T6 [43]*Driving impairment*, measured using Attention-Related Driving Errors Scale (ARDES) [44] at T1–T6*Birthing and obstetric outcomes*, measured by self-report at T3 and by medical record extraction for participants who have provided consent and are patients at Monash Health or Royal Women’s Hospital*Birthing parent mental health*, measured by PROMIS Anxiety (CAT Version) [34] at T1–T6, PROMIS Meaning and Purpose (CAT Version) [45] at T1–T6 and *positive affect*, as measured by Positive and Negative Affect Scale [46] at T1–T6*Relationship satisfaction*, measured by brief Dyadic Adjustment Scale [47] for participants who have a current partner, at T1–T6*Sexual Satisfactions*, as measured by questions “How often in the past 30 days have you engaged in any sexual activity (either with a partner or yourself)?” and “Over the past 30 days, how satisfied have you been with your sex life overall?”, adapted from PROMIS Sexual Function and Satisfaction [48], at T1–T6.

#### Other factors

The following are included to provide contextual information about the sample and for their potential role in treatment response:*Demographic and medical conditions information* will be collected by self-report.*Social support* as measured by PROMIS Instrumental & Emotional Support (CAT Version) [49] at T1–T6*Chronotype* as measured by Reduced Morningness Eveningness Questionnaire (RMEQ) [50] at T1–T6*Infant sleep (sleep onset latency, night-time awakening, daytime sleep duration, night-time sleep duration, nap duration,* etc.*)*, as measured by Brief Infant Sleep Questionnaire (BISQ) [51] at T3–T6*Patient capability, opportunity and motivation for behaviour change*, as measured by brief Capability, Opportunity, Motivation - Behaviour (COM-B) questionnaire [52] at T2 and T4*Patients’ perceived credibility and expectancy of treatment*, as measured by the Credibility Expectancy Questionnaire (CEQ) [53] at T1*Stress vulnerability*, as measured by Ford Insomnia Response to Stress Test (FIRST) [54] at T1–T6*Beliefs and attitudes about sleep*, as measured by Dysfunctional Beliefs and Attitudes about Sleep Scale (DBAS-16) at T1–T6 [55]*Physical activity*, as measured by International Physical Activity Questionnaire Short Form (IPAQ-SF) [56] at T1–T6*Attitude toward eating*, as measured by Eating Attitude Test Short Form (EAT-8) [57] at T1–T6*Food security*, as measured by United States Department of Agriculture (USDA) Household Food Security Survey Short Form (T1) and Long Form (T4, T5, T6) [58]

### Harms {17}

Participants will complete an adverse event checklist [39] and report any hospitalisations at each timepoint following randomisation. Participants are also encouraged to contact the research team if any adverse events happen.

The following three levels of risk and adverse events are considered:

## Mental health-related risk

These are defined as intense psychological distress that may cause significant impairment to everyday functioning or impose risk to self or others (see Mental health risk protocol, supplementary material).

## Side effects

These are assessed at each post-baseline timepoint using an adverse events checklist for sleep interventions [39], which lists adverse effects that may (e.g. sleepiness) or may not (e.g. headaches) be the result of the intervention. Findings on these measures will be reviewed by the Data Safety Management Board (DSMB) at planned meetings. Participants will also be asked to contact the research team immediately if they experience any side effects that they may be attributing to the intervention.

## Severe adverse events

These are defined as maternal or infant deaths or serious complications that require hospitalisation (i.e. admission to ward). These events are reported at each assessment timepoint, and participants are encouraged to notify immediately if they have occurred. Expected events such as hospitalisation related to childbirth will be excluded from review.

Two investigators, one expert in sleep medicine and the other an obstetrician, will review all serious adverse events (SAEs) upon reporting and assess their expectedness and whether they may be related to the intervention. If any SAEs were suspected to be related to the intervention, the chair of the DSMB will be notified within 48 h. The chair will then decide whether an ad hoc meeting of the DSMB should be held. Harms will be analysed and reported in line with MedDRA structured vocabulary. Adverse events which are deemed to be potentially related to the intervention will be reported in trial publications.

### Participant timeline {18}

An overview of the participant timeline for those randomised in the trial is provided in Fig. 2.

### Sample size {19}

Sample size calculations for the present trial were informed by statistical, empirical, and clinical considerations, given cautions on basing power solely on pilot data [59]. Factors considered were as follows: (1) In a previous trial [21], Cohen’s d effect sizes for ISI and sleep-related impairment in women with baseline elevated ISI (> 7) ranged from 0.43 to 1.15. (2) Trial investigators with clinical experience discussed the smallest meaningful effect and identified a Cohen’s d = 0.40. (3) We calculated bootstrap confidence intervals for Cohen’s d from the previous trial data. Results showed that in > 75% of the time, the pilot effect size was Cohen’s d > 0.40, bolstering confidence that this clinically meaningful effect is highly plausible from our intervention.

For the effectiveness component of this trial, there are two primary outcomes (ISI at T2 and average ISI across T3–T5) and two secondary outcomes (SRI at T2 and average SRI across T3–T5) for a total of four hypothesis tests across primary and secondary outcomes. A Bonferroni correction for four tests would be *α* = 0.05/4 = 0.0125. We rounded down and conservatively set *α* = 0.01, two-tailed to adjust for multiple comparisons.

Planned primary and secondary analyses are four linear regression analyses, one for each outcome. Collectively, the models will have the following parameters estimated: 1 for the intercept, 1 for covarying for the outcome at baseline, 1 for the dummy-coded treatment condition, and 15 for the dummy-coded strata (see the “Sequence generation {21a} and {21b}” section for all 16 unique strata) resulting in a total of 18 estimated coefficients. For the pilot and for identifying a clinically important difference, we used Cohen’s d effect size. However, analyses are linear regressions to allow for covariates, so for power analyses, we translated Cohen’s *d* = 0.40 to a Cohen’s f2 of 0.04 using Cohen’s formula [60]:$${f}^{2}={\left(\frac{d}{2}\right)}^{2}$$

We used the pwr.f2.test() function from the R package pwr to calculate the required sample size for the following conditions:Two-tailed *α* = 0.01.One numerator degree of freedom, testing the dummy-coded treatment condition85% power10% dropout (90% retained)18 degrees of freedom used up in the regression models

A further sample size consideration is the stratified randomisation. We have 16 total strata (see the “Sequence generation {21a} and {21b}” section for details). A rule of thumb [61] for stratified randomisation using permuted blocks is that the number of strata should be no more than N/(4 × block size). As we are using a big stick design (BSD) for randomisation with maximally tolerated imbalance (MTI) = 2, the block size approach does not directly apply. However, a *MTI* = 2 for a two-group design yields the same possible maximum imbalance as permuted blocks with block size *B* = 4. Using this rule of thumb gives us a minimum required sample size to prevent overstratification of *N* = 16 × 16 = 256. Power analyses showed that a sample size of *N* = 384 provides ≥ 85% power to detect a Cohen’s *d* = 0.40 (Cohen’s f2 = 0.04) with two-tailed *α* = 0.01 to account for multiple comparisons and the outcome variable at baseline and all strata included as covariates. This also exceeds the minimum sample size needed for 16 strata. Thus, the final planned sample size was *N* = 384.

#### Updated increased sample size

When recruitment of the proposed sample size (*N* = 384) was complete, attrition and completeness of data were considered to assess the appropriateness of the sample size. Completion rates for T2, T3, and T4 varied between 74% and 84%, which was lower than the anticipated 90%. To account for this increased attrition, an increased sample size was required. The additional participant calculation is based on the following: If 70% of the sample completes at least 2 postpartum timepoints, a sample of 346/0.70 = 495 is needed; this is 111 more than planned. Thus, an increased proposed sample size of *N* = 495 is needed to account for potential impacts of attrition.

### Recruitment {20}

For public hospital recruitment, research midwives at Monash Health and the Royal Women’s Hospital will contact (via text message, phone call, e-mail, flyer, or in person at antenatal clinics) potentially eligible individuals. For online recruitment, online advertising will be conducted through social media and online newsletters. Recruitment will also be conducted in the community through study flyers in public areas (e.g. medical clinics and baby fairs).

When visiting the sign-up link, participants will be provided with a brief summary of information about the study. Participants are then able to assess their eligibility based on their gestation, age, and whether they live in Australia. If the potential participant is within 26–32 weeks of gestation, they will be invited to consent immediately; if a potential participant is less than 26 weeks of gestation, they will receive an e-mail inviting them to participate when they reach 26 weeks of gestation.

## Assignment of interventions: randomisation

### Sequence generation {21a} and {21b}

The random allocation sequence was developed by the trial statistician. Eligible participants will be randomised using a complete randomisation scheme generated in advance and conducted via REDCap [27, 28].

Randomisation will be stratified by the following:Recruitment source (hospital patient coded as 0, other community recruitment coded as 1)Insomnia severity (low < 14 coded as 0, high ≥ 14 coded as 1)Gravidity (first pregnancy coded as 0, second or more coded as 1)Baseline PROMIS depression symptoms (low ≤ 50 coded as 0, high > 50 coded as 1)

Fully crossed, this results in 2 × 2 × 2 × 2 = 16 unique strata. There are many algorithms to generate random sequences. Simple complete randomisation involves a fully random process, but this does not guarantee balance between the trial arms for a fixed sample size and may, by random chance, introduce time effects (e.g. theoretically it is possible, albeit unlikely, that the first 50% of participants are all randomised to intervention and the next 50% all to control). The permuted block randomisation (PBR) is perhaps the most common solution to this in clinical trials. PBR guarantees balance at the end of each block. However, the PBR introduces a new risk which is that it is predictable (e.g. in a block size of 4, if two people have been randomised to control, the researcher knows that the next two people will be randomised to intervention). BSD is another method of generating a random sequence that can be harder to guess and is theoretically superior to PBR [62]. To ensure a degree of balance, it is possible to specify the MTI. The MTI reflects the biggest sample size difference tolerated between conditions within the randomly generated sequence. We evaluated seven algorithms based on two properties: (1) The maximum imbalance observed during the sequence and (2) the probability of a correct guess, assuming the guess is based on whichever group is currently smaller. In both cases, lower is better reflecting less imbalance and a lower probability that the researcher may correctly guess, and thus bias, the next randomisation. We evaluated seven algorithms for randomisation using 10,000 randomly simulated sequences; these were as follows: (1) complete randomisation, (2) PBR, (3) random PBR (RPBR), (4) maximal procedure (MP), (5) BSD, (6) Efron’s biased coin design (EBCD), and (7) Chen’s design (CD). For each, we evaluated conditions with sequence length 100 and varying: (1) MTI of 2 and 4 for MP, BSD, and CD; (2) probability = 0.6 and 0.8 for EBCD and CD; (3) probability block size = 4, 6, and 8 for PBR; and (4) random blocks of size 4, 6, or 8 for RPBR. Results of these simulations revealed that for our purposes, the BSD with *MTI* = 2 provided optimal balance between minimising imbalance and reducing the probability that a researcher could correctly guess the next allocation. Therefore, we use BSD with *MTI* = 2.

### Allocation concealment mechanism {22}

Following confirmation of eligibility, the study staff will be able to randomise participants via the REDCap randomisation function. The randomisation allocation cannot be changed by staff either prior to or after randomisation. Staff will not be able to see the allocation sequence prior to randomisation being complete.

### Implementation {23}

The randomisation sequence will be built into REDCap [27, 28] by the trial statistician prior to the enrolment of the first participant. Randomisation will be conducted through REDCap by a trained research team member. The randomisation sequence cannot be accessed by staff members who are conducting the randomisation.

## Assignment of interventions: blinding

### Who will be blinded {24a}

Given the nature of the interventions, it is not possible for participants to be blind to their treatment allocation, but the condition pseudonyms “Group A” and “Group B” are used to avoid bias. As randomisation is completed by the research team and is necessary for administrative purposes, the study coordinator, research assistants, and clinicians will not be blinded to the group allocation. The chief investigator will be blinded to the group allocation except in exceptional circumstances where the risk to participants outweighs the benefit of blinding, such as evaluating a serious adverse event. Statisticians will not be blind to the condition in order to facilitate the conduction of statistical analysis.

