## Statistical methods

### Statistical methods for primary and secondary outcomes {27a}, {27b} and {27c}

A detailed descriptive profile will be created for all outcomes, intervention conditions, sample characteristics, and intervention adherence. Descriptive statistics will be as follows: (1) For continuous variables that are approximately normally distributed without outliers: mean and standard deviation; (2) for continuous variables that are not normally distributed or have outliers: median and interquartile range; and (3) for discrete variables: frequency and percentage.

We will report the frequency and percent of participants who completed each timepoint and who have missing data at each timepoint. Adverse event frequency and type will be reported with frequencies and percentages. We will compare the proportion of withdrawn or missing participants at each timepoint and the proportion of adverse events by condition using chi-squared tests.

#### Effectiveness for Aim 1

To test aim 1, which is ISI (primary) and SRI (secondary) will be lower in the Healthy Sleep Program than the Control condition, we will use regression analyses. Analyses will be intention to treat, with participants analysed in the condition to which they were assigned regardless of actual intervention receipt. Significance is set at *α* = 0.01, two-tailed. We will calculate the expected raw difference in outcomes between treatment and control with 95% confidence intervals, along with the standardised difference to measure the effect size. All effectiveness analyses for Aim 1 will be conducted in R.

The dual primary (ISI at pregnancy and postpartum) and two secondary (SRI at pregnancy and postpartum) outcomes will be used as described previously (see “Outcomes {16}”) with the outcomes treated as continuous variables. Analyses will be separate regressions for each outcome, with the outcome as the dependent variable. Treatment condition will be dummy coded (Healthy Sleep Program = 1, sleep hygiene education = 0) and included as the focal predictor. The outcome measure at baseline (T1) will be included as a covariate. That is, ISI at T1 will be included for both ISI primary outcomes, and the SRI at T1 will be included for both SRI secondary outcomes. Randomisation strata will be fully crossed and dummy coded, and these dummy codes will be included as covariates [61]. The method selected for statistical inference for the main analyses will depend on features of the data.

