If outcome data are missing, we will use multiple imputation through chained equations (MICE, [63]) based on predictive mean matching (PMM; [64]). We will generate 100 imputed datasets.

*Second*, if model residuals are approximately normally distributed, we will use normal theory-based standard errors to calculate confidence intervals and *p*-values. If model residuals are not normally distributed, we will use a nonparametric bootstrap with percentile-based confidence intervals based on 20,000 bootstrap samples. In this case, in addition to reporting 95% confidence intervals, we will use the 99% bootstrap percentile intervals to determine statistical significance based on whether or not the interval includes 0. The distribution of model residuals will be determined by fitting a linear regression model and creating a density plot of the residuals and a Q-Q plot of the observed residuals against a normal distribution.

*Third*, if there are no outliers in the model residuals, we will use regular linear regression. If there are outliers in the model residuals, we will use quantile regression and use a median (50th percentile) estimator. Outliers in the residuals will be determined by fitting a linear regression model, extracting the residuals and creating a density and rug plot.

The above choices will be combined as necessary based on the data. For example, if outcome data are missing, the residuals demonstrate non-normality and there are outliers, we would use quantile regression, non-parametric bootstrapping and multiple imputation. In cases where we use both bootstrapping and multiple imputation, we will use the approach of bootstrapping in the outer loop and then using imputation in the inner loop [65]. That is, for each of 20,000 bootstrap samples, we will use MICE with PMM to generate a single imputed dataset with added noise reflecting the uncertainty of the imputation, resulting in a total of 20,000 datasets that are both bootstrapped and imputed. This was selected as a simulation study demonstrated that while it is computationally demanding, it provides the best validity [65].

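### Statisticians who know the arms choose the primary estimator and inference method by eye, and nothing says the choice is locked before the treatment effect is seen

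*Protocol article*

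**What the plan says.** **Blinding.** Section *Who will be blinded {24a}* states: "Statisticians will not be blind to the condition in order to facilitate the conduction of statistical analysis". Ease of analysis is the only reason given. The same section says "The chief investigator will be blinded to the group allocation except in exceptional circumstances". It also says that "condition pseudonyms “Group A” and “Group B” are used to avoid bias", but mentions these labels only for participants.

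**Allocation.** Section *Sequence generation {21a} and {21b}* says: "The random allocation sequence was developed by the trial statistician". Section *Implementation {23}* has the same role load the sequence into REDCap.

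**Choice of method.** In the statistical methods section, under *Effectiveness for Aim 1*: "The method selected for statistical inference for the main analyses will depend on features of the data". There are two visual switches:

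- Normality is judged by "creating a density plot of the residuals and a Q-Q plot of the observed residuals against a normal distribution". The consequence is: "If model residuals are not normally distributed, we will use a nonparametric bootstrap with percentile-based confidence intervals based on 20,000 bootstrap samples".
- "Outliers in the residuals will be determined by fitting a linear regression model, extracting the residuals and creating a density and rug plot". If outliers are found, linear regression gives way to median regression.

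Neither switch has a numerical threshold. The article does not say who inspects the plots, or that the branch is settled before the treatment coefficient is seen. Section *Protocol and statistical analysis plan {5}* says that the analysis plan is contained in the article.

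**The concern.** An unblinded statistician matters little when the primary model is fixed in advance. Here it is not fixed. The outlier switch changes the quantity estimated, from a difference in means to a difference in medians, and the normality switch changes how significance is decided.

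The residuals come from a fitted linear regression. If that is the planned model, with treatment coded 1 for the Healthy Sleep Program, the labelled treatment coefficient already exists when the plots are read. An analyst who has seen the result under each branch can lean towards the more convincing one without intending to. This applies to both ISI endpoints and both SRI endpoints.

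The stated reason does not require unblinding either. Regression, imputation, bootstrap and residual checks all run identically on a neutral two-level code.

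**Working it through.** **1. The plan's own figure.** The article's inputs are f² = 0.04, two-sided alpha 0.01, one numerator degree of freedom, 18 coefficients and 85% power. With u = 1, v = N − 18 and noncentrality λ = f²(u + v + 1), the smallest N with at least 85% power is 346: v = 328, λ = 0.04 × 330 = 13.2, power 0.8506. Then 346/0.90 = 384.4 (384 stated) and 346/0.70 = 494.3 (495 stated). The sample size reproduces and this point does not affect it. The figure of 346 evaluable participants is used below.

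**2. Worst-case error under no effect.** The simulated model has n = 346, equal arms, one baseline covariate and residual SD 1. Each data set is analysed by linear and by median regression, and the analyst keeps the smaller p-value. The table gives the share of runs with two-sided p < 0.01.

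| Residuals | Runs | Linear, fixed | Median, fixed | Smaller p of the two |
|---|---|---|---|---|
| Normal | 5,000 | 1.16% | 0.70% | 1.58% |
| t, 4 df | 5,000 | 0.94% | 0.68% | 1.48% |
| Skewed (chi-square, 4 df) | 5,000 | 1.10% | 1.32% | 2.14% |
| Normal | 6,000 | 1.07% | 0.65% | 1.47% |
| Skewed (chi-square, 4 df) | 6,000 | 1.18% | 0.98% | 1.98% |

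A separate run of 3,000 gave 1.6% (normal) and 1.9% (gamma residuals). The Monte Carlo standard error in the 6,000-run rows is √(0.0147 × 0.9853/6000) = 0.16 points and √(0.0198 × 0.9802/6000) = 0.18 points. Measured against the simulated fixed linear analysis, the excess in those rows is 1.47 − 1.07 = 0.40 and 1.98 − 1.18 = 0.80 points.

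**3. What masking alone changes.** Swapping the arm labels turns the coefficient b into −b and leaves its standard error alone, so |b/SE| and the two-sided p-value are unchanged. An analyst with neutral codes can therefore still pick the smaller p. The 6,000-run simulation compared an unblinded analyst who picks the result more favourable to the intervention with a masked analyst who picks the smaller p:

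| Setting | Quantity | Linear, fixed | Unblinded, favourable | Masked, smaller p |
|---|---|---|---|---|
| No effect, normal | False claim of benefit (nominal 0.50%) | 0.42% | 0.58% | 0.58% |
| No effect, skewed | False claim of benefit (nominal 0.50%) | 0.63% | 0.98% | 0.98% |
| No effect, normal | Mean estimate (SD) | 0.00 | −0.029 | 0.00 |
| No effect, skewed | Mean estimate (SD) | 0.00 | −0.033 | 0.00 |
| d = 0.40, normal | Mean estimate (SD) | −0.401 | −0.414 | −0.414 |
| d = 0.40, skewed | Mean estimate (SD) | −0.401 | −0.427 | −0.427 |

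Masking removes the shift of about 0.03 SD under no effect. It leaves the rate of false benefit claims unchanged. It also leaves the overestimate at d = 0.40, which is 0.414 − 0.401 = 0.013 SD with normal and 0.427 − 0.401 = 0.026 SD with skewed residuals.

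**4. What follows for the remedy.** The inflation comes from seeing the results before choosing. It stops only if the branch is fixed while the treatment coefficients and p-values are still unseen.

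**The case against.** The strongest reply is that the blinding section contains no error. It discloses openly who is unblinded and why, and the branches are prespecified and tied to residual diagnostics, not to the treatment result. The simulation replaces that rule with free choice on p-values, which the plan does not permit. It also leaves out the 15 stratum terms, the imputation and the bootstrap option. All of this stands, and it is why the figures are a worst case for one two-way choice and not a forecast.

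A reader might also infer that blinding the statistician would by itself remove the bias at almost no cost. The documents and the calculation do not support that. Neutral codes leave the two-sided error and the overestimate under a true effect where they were. Masking is also imperfect here. The trial statistician generated the sequence, the model needs baseline scores and all 16 strata, which could allow relinking, and the adherence data for the complier analysis reveal the arm.

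Finally, it can be said that the real problem is the visual triggers. That is largely so, but a lock before sight of the estimate is a separate safeguard and works even if the triggers stay visual.

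**Conclusion.** The point holds as an avoidable risk in all four confirmatory tests. It arises from three features together: statisticians who know the arms, branch choices made by eye, and no stated order between that choice and sight of the treatment effect. If results under both regressions were seen first and the more significant one kept, the nominal 1% two-sided error would become about 1.5–2%. This assumes 346 evaluable participants, one baseline covariate and the residual shapes listed above.

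The article does not show that any such selection has occurred or is intended, so it would be wrong to conclude that the results will be biased or that the 0.01 level is already lost. This is a cheap improvement to the plan's credibility and not a fatal flaw.

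**What to change.** Replace the sentence on statisticians in *Who will be blinded {24a}* with a rule of this kind:

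> For each of the four primary and secondary outcomes, the outlier and normality branch will be selected from residual plots on a file with neutral arm codes and scrambled IDs. A team member other than the trial statistician will prepare this file, with treatment coefficients and p-values suppressed. The selection will be signed and dated before any treatment estimate or arm label is released. Session and adherence data will be withheld until then, and the complier analysis will follow release.

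The second team member can make suppression practical by running the diagnostic fit and handing over only the residuals and plots. Imputation should not be listed as a discretionary branch, because missing outcome data trigger it automatically. Fixing one estimator in advance, or giving numerical triggers, would reduce the discretion at its source and can be done as well.

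**Cost.** One recoded export by a second existing team member, one sign-off and a short delay. Masking stays imperfect because of possible relinking. Sample size, alpha and power do not change.

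**Timing.** Data collection is ongoing, the last follow-up is planned for about 01/03/2027, and no interim analyses were planned. The four endpoints need data only to 12 months postpartum, which is 24 − 12 = 12 months before that last visit, or about March 2026. The lock must therefore precede the first Aim 1 analysis, not merely the end of follow-up.
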